### Sample size and power analysis

At least 3000 participants will be recruited for the cross-sectional study from which 400 cases and 400 matched controls will be selected for the case-control sub-study. The sample size was calculated based on the following assumptions. Utilising 1000 Genomes data, we estimated the minor allele frequency (MAF) within the population, using the Yoruba in Ibadan (Nigeria) as a proxy for our study population [26]. The rare polymorphism, rs9349256 has the lowest MAF of 0.01 while the common polymorphism, rs717620 has the highest MAF of 0.42, the average MAF being 0.19. In addition, a Bonferroni correction was incorporated by setting our alpha level at 0.003 (0.05/18) to account for the multiple comparison testing. With the aid of a web browser program for basic sample size calculations of single nucleotide polymorphism (SNP) studies [27–29] [http://biostats.usc.edu/Quanto.html] and using a dominant inheritance model, the average MAF of 0.19, 13% KTD prevalence [30], a power of 80% and an alpha of 0.003, a sample size of 400 cases and 400 controls is able to detect a minimum odd ratio (OR) of 1.75 (case control phase). Table 1 indicates the required sample size (per group using a dominant model) to detect different odds ratios. Based on the data from a previous study in Nigerian PLWHIV which reported the prevalence of TDF-induced KTD as 13%, we made an assumption that 13% of TDF-treated individuals will develop KTD [30]. Therefore, taking this into consideration, the number needed to be screened to identify 400 cases is approximately 3000. We will therefore screen 3000 participants in the cross-sectional phase of this study.

**Table 1 Tab1:** Calculations of the sample size (per group using a dominant model), required to detect different odds ratios in case-control analysis, assuming alpha = 0.003; power = 80% and ratio cases/controls = 1

Odds ratio	Sample Size (N)
1.25	2531
1.50	760
1.75	398
2.00	260
2.25	191
2.50	150
2.75	124
3.00	106

Simulated trials to determine the power we have to detect our smallest and our largest MAFs, using a dominant inheritance model, and an alpha of 0.003, and a sample size of 400 showed that we are quite underpowered for the SNP with the lowest MAF; only able to reliably (power = 80%) find differences with an OR of 5 or greater. However, there is only one SNP with such a low MAF, and for the second lowest (MAF = 0.03) we have sufficient power to detect OR of 2.75 or greater. For the SNP with MAF = 0.42, we are powered to detect OR of just greater than 1.75 (Fig. 1).

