### Statistical analysis

Descriptive results of continuous variables will be expressed as medians and interquartile ranges. Continuous variables will be tested for normality using the Shapiro–Wilk test and compared using the student’s *t* test or Wilcoxon rank sum test, as required. For the comparison of proportions, the Chi-square test will be used, with Fisher’s corrections applied when needed. Multivariate logistic regression analyses will be performed to identify factors associated with KTD. Parameters with significant *p*-values in the univariate analysis will be entered into a stepwise multivariate analysis. Deviations from Hardy-Weinberg equilibrium of individual alleles and differences in allele frequencies between the two groups will be evaluated by either the chi-square test or Fisher’s exact test where appropriate. Statistical comparisons for genotype frequencies between persons with KTD and those without KTD will be made by the chi-square test or Fisher’s exact test. Associations between allele sets or haplotypes and the risk of TDF-induced KTD will be estimated by computing odds ratios and 95% confidence intervals from multivariable logistic regressions. This analysis will include adjustments for demographic characteristics (age, sex, and BMI), baseline eGFR, duration of HIV infection, protease inhibitor therapy, and other antiretroviral treatment. All statistical analyses will be conducted using Stata 12 and R statistical software. *P* values < 0.05 will be considered statistically significant. Methods for controlling the false discovery rate and Bayesian analysis under shrinkage priors will be used when reporting the results of multivariable logistic regression.

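### The primary SNP association is powered for a dominant carrier test, but the analysis section lists allele, genotype and haplotype analyses, with no dominant coding and none named primary

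*Protocol article*

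**What the plan says.** The Methods/design section of the protocol article makes SNP association a primary outcome, alongside KTD prevalence.

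- **Sizing.** The Sample size and power analysis section works "using a dominant inheritance model, the average MAF of 0.19, 13% KTD prevalence [30], a power of 80% and an alpha of 0.003". The alpha comes from "setting our alpha level at 0.003 (0.05/18) to account for the multiple comparison testing", which is one test for each of 18 SNPs. The Table 1 caption repeats the dominant model, and the table gives 398 per group at OR 1.75.
- **Power across allele frequencies.** The simulations for the rarest and commonest SNPs are also run "using a dominant inheritance model, and an alpha of 0.003, and a sample size of 400". For the commonest SNP the text concludes: "For the SNP with MAF = 0.42, we are powered to detect OR of just greater than 1.75".
- **Analysis.** The Statistical analysis section says that "differences in allele frequencies between the two groups will be evaluated by either the chi-square test" or Fisher's exact test. It adds: "Statistical comparisons for genotype frequencies between persons with KTD and those without KTD will be made by the chi-square test" or Fisher's exact test. Allele sets or haplotypes go into multivariable logistic regression. A dominant model is not mentioned in this section, no genotype coding is given, and no analysis is named as the primary SNP test.

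**The concern.** A power figure belongs to a particular test. The figure here belongs to a 1-df comparison of carriers with non-carriers of the minor allele. The allele test instead counts chromosomes, so it dilutes an effect that is the same for one copy as for two. A genotype test over three genotypes spends a second degree of freedom. If the assumed dominant effect is true, both have less power than the article states. The Bonferroni level also allows for one test per SNP while at least two are listed, and with no primary coding named, the coding to report can be chosen after the data are seen. The point concerns the 15 transporter SNPs in Table 2; how APOL1 should be coded is a separate question.

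**Working it through.** **Inputs, all from Sample size and power analysis:** 400 cases and 400 controls, alpha 0.003, OR 1.75, prevalence 13%, MAF 0.19 (average) and 0.42 (highest). Assumed: two-sided tests and Hardy-Weinberg proportions in the source population.

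**1. Carrier proportions.** At MAF 0.19 the genotype shares are 0.81², 2 × 0.19 × 0.81 and 0.19². Applying a dominant OR of 1.75 at 13% overall prevalence gives carriers of 0.4592 in cases (p1) and 0.3267 in controls (p0).

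**2. Reproduce the plan's figure.** With p̄ = (p1 + p0)/2 = 0.393, z = 2.968 for two-sided alpha 0.003 and z = 0.842 for 80% power:

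n = [2.968 √(2p̄(1−p̄)) + 0.842 √(p1(1−p1) + p0(1−p0))]² / (p1−p0)² = (2.050 + 0.576)² / 0.1325² ≈ **393 per group**.

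A matched-pair version uses the discordant probabilities p1(1−p0) = 0.309 and p0(1−p1) = 0.177, which sum to 0.486:

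n = [2.968 √0.486 + 0.842 √(0.486 − 0.1325²)]² / 0.1325² ≈ **398**.

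The matched-pair formula also reproduces every row of Table 1 to within 1. The sizing arithmetic is therefore right for a dominant 1-df test. A one-sided version gives 349 and does not fit.

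**3. Same truth, listed tests, MAF 0.19.** Power is the upper tail of a non-central chi-square beyond the 0.003 critical value (8.81 for 1 df, 11.62 for 2 df).

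- Carrier test: λ = 400 × 0.1325² / (2 × 0.393 × 0.607) = 14.7; 1 df; power 81%.
- Genotype 2 × 3 test: λ is the same 14.7, because under a dominant effect splitting carriers into one and two copies adds no information. With 2 df, power is 72%.
- Allele test: minor allele shares are 0.2537 and 0.1805 (mean 0.217); λ = 800 × 0.0732² / (2 × 0.217 × 0.783) = 12.6; 1 df; power 72%.

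A check with 40,000 simulated data sets gave 81%, 72% and 73%.

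For 80% power the required λ is 14.5 (1 df) or 16.9 (2 df). The genotype and allele tests therefore need about 460 per group, or an OR of about 1.82 with 400 per group.

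**4. MAF 0.42, the commonest SNP.**

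| Test | Power at dominant OR 1.75 | OR detectable with 80% power |
|---|---|---|
| Carrier, 1 df | 73% | 1.82 |
| Genotype, 2 df | 62% | 1.92 |
| Allele, 1 df | 48% | 2.13 |

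The genotype value is 1.91 by a likelihood-ratio calculation and 1.92 by Pearson chi-square. The carrier value of 1.82 fits the article's statement for this SNP; the other two do not.

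**5. If the effect is additive instead.** At MAF 0.19 and a per-allele OR of 1.75, power is 91% carrier, 91% genotype and 95% allele. At MAF 0.42 and a per-allele OR of 1.5 it is 65%, 77% and 85%.

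**6. Two tests per SNP.** Simulated with no association, the chance that the allele or the genotype test falls below 0.003 is about 0.0047 per SNP. Over 18 SNPs this bounds the family-wise error at 18 × 0.0047 = 0.085. One test per SNP gives 18 × 0.003 = 0.054.

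Haplotype power cannot be computed, because the article gives no haplotype frequencies.

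**The case against.** **The plan may still run the dominant test.** A reader might infer that the powered test is not run at all. The text does not support that. It fixes no table dimensions for the genotype comparison and no coding for the regression. A carrier comparison is also a chi-square on genotypes, and an analysis plan that is not shown may specify it. This stands as a limit: what can be said is that no dominant test is stated. It does not remove the point, because an allele-frequency comparison cannot be read as a carrier test and nothing identifies which listed analysis is the powered one.

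**The listed tests are not always weaker.** This stands. The shortfall holds only if the effect is dominant, and step 5 shows the order reversing under additivity. But the article chose the dominant model for its power claim, so the claim should hold for that model with the planned test.

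**At the stated threshold there is no shortfall.** The Statistical analysis section uses P < 0.05. At that level power at MAF 0.19 is about 97%, 94% and 95% for the three tests. True, but that drops the Bonferroni level on which the study was sized and so cannot support the stated 80%. Which threshold applies is a separate matter.

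**Thirty-six looks.** Counting two tests for each of 18 SNPs suggests a doubled error rate. The two tests are strongly correlated, so the excess is moderate (step 6), and false-discovery-rate control and shrinkage priors are planned for the multivariable models.

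**The loss is modest at the planning MAF.** It is, at about 9 points. For rare SNPs the allele test loses almost nothing: at MAF 0.03 and OR 2.75 it has 78% against 79% for the carrier test.

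**Conclusion.** The point holds as a mismatch between the power statement and the stated analyses. The 400 + 400 sizing is correct for a dominant 1-df test. For the 2-df genotype and allele tests, the same design gives about 72% power at OR 1.75 and MAF 0.19, with 80% reached at about 1.82. At MAF 0.42 the detectable OR rises from about 1.82 to 1.92 (genotype) or 2.13 (allele).

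These figures assume a dominant effect, alpha 0.003, 13% prevalence, Hardy-Weinberg proportions, and a genotype comparison over three genotypes without collapsing. They do not show that the sample size was miscalculated or that the dominant test is the better choice. The matter should be put right because it affects a primary outcome and leaves the choice of coding open.

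**What to change.** In the Statistical analysis section, name one primary test and coding for each transporter SNP, and label the other SNP analyses as supporting. Then make the power statement match, in one of two ways:

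1. **Carrier test primary.** State a 1-df comparison of carriers with non-carriers of the minor allele. The Sample size and power analysis section can stay as it is. The cost is less power for additive effects (65% against 85% for the allele test at MAF 0.42 and a per-allele OR of 1.5) and almost none for recessive effects, which only the supporting analyses could pick up.
2. **Genotype or allele test primary.** Restate the main power figure as about 72% at a dominant OR of 1.75, with 80% at about 1.82. Restate the detectable OR at MAF 0.42 as about 1.92 (genotype) or 2.13 (allele). Table 1 would need recomputing for the chosen test.

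Either way, naming a single primary test restores the one-test-per-SNP basis of the Bonferroni level. The first option takes a sentence or two; the second also takes revised power figures. Neither needs more data.

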**Fig. 1 Fig1:**
[figure not shown]
Model showing relationship between MAFs, odds ratio and power (*N* = 400)

### Recruitment of participants

An outline of how participants will be recruited for this study is shown in the study flow chart in Fig. 2. After obtaining patient consent, case report forms will be completed for all participants and will include the following data:
Demographics - Age, sex, body weight, body mass indexPast medical history - history of AIDS, route of HIV transmission, specific combination of ART, duration of therapy, history of tobacco use, hypertension, diabetes mellitus, congestive cardiac failure, co-infection with hepatitis B and C, concurrent use of ritonavir-boosted protease inhibitors, concurrent use of nephrotoxic drugs, such as ganciclovir and sulfamethoxazole/trimethoprim.Baseline laboratory data - CD4 count, HIV viral load, serum creatinine and estimated glomerular filtration rate (eGFR). As recommended by the National Kidney Foundation, eGFR will be calculated using the CKD-EPI formula [31].

**Fig. 2 Fig2:**
[figure not shown]
Study flow chart

### Diagnostic criteria for KTD

Kidney tubular dysfunction will be defined by the presence of at least 2 of the following abnormalities, with at least 1 being a Fanconi syndrome criterion (glucosuria in nondiabetic individuals or hyperphosphaturia) [32].
Nondiabetic glucosuria (urine glucose level ≥ 300 mg/dL daily)Total excretion of phosphorus (urine phosphorus X urine volume) > 1200 mg dailyFractional tubular resorption of phosphorus (1- [(urine phosphorus X plasma creatinine)/(plasma phosphorus X urine creatinine)]) < 0.82Fractional excretion of uric acid ([(urine uric acid X plasma creatinine)/(urine creatinine X plasma uric acid)] X 100) > 15%Proteinuria > 0.2 g/24 h.

### Laboratory procedures

Blood and urine samples will be collected for routine laboratory measurements and the measurement of markers of renal function and proximal tubulopathy. The latter tests will be performed by LTH clinical laboratory services using an ADVIA® 1800 Chemistry System (Siemens, Germany). Blood samples will be used for creatinine, urea, electrolyte, uric acid and glucose measurements. Serum creatinine will be measured using the Jaffe method. A 24-h urine sample will be collected to measure protein, glucose, phosphate, uric acid and creatinine. Participants will be fasted overnight for at least 8 h and allowed to drink ad libitum. Spot urine samples will be collected and stored at − 80 °C for urinary RBP and NAG analysis using the RBP Urinary Competitive ELISA kit (ThermoFisher Scientific) and NAG ELISA Kit (R&D Systems, Inc. Minneapolis, USA).

An additional blood sample will be drawn for genomic DNA extraction. Samples will be collected into ethylenediaminetetraacetic acid (EDTA) vacutainers and stored at − 20 °C until DNA extraction. Genomic DNA will be extracted from the whole blood and the concentrations determined using a Qubit fluorometer (Thermo Fisher Scientific). DNA will be aliquoted and stored at − 80 °C.

The 18 SNPs to be genotyped are outlined in Table 2. Candidate SNPs were selected based on previously reported functional significance and minor allele frequencies > 5% in the literature [16, 32, 33]. SNPs will be genotyped using the rhAmp SNP Genotyping Assays. The rhAmp SNP assays provide a highly accurate, PCR-based genotyping method. The method is based on RNase H2-dependent PCR (rhPCR) and has improved specificity over TaqMan and KASP technologies [34]. The SNP genotyping will be carried out at the Internal Medicine Research Laboratory, University of Witwatersrand, South Africa.

**Table 2 Tab2:** List of selected Single Nucleotide Polymorphisms

SNP	Gene	Chromosome	Position	Alleles
rs717620	ABCC2	Chromosome 10	99782821	C > T
rs2273697	ABCC2	Chromosome 10	99804058	G > A
rs17222723	ABCC2	Chromosome 10	99836239	T > A
rs3740066	ABCC2	Chromosome 10	99844450	C > T
rs8187710	ABCC2	Chromosome 10	99851537	G > A
rs899494	ABCC4	Chromosome 13	95209550	G > A
rs1751034	ABCC4	Chromosome 13	95062722	T > C
rs3742106	ABCC4	Chromosome 13	95021537	A > C
rs9349256	ABCC10	Chromosome 6	43404511	G > A
rs2125739	ABCC10	Chromosome 6	43445127	T > C
rs1045642	ABCB1	Chromosome 7	87509329	C > T
rs1128503	ABCB1	Chromosome 7	87550285	C > T
rs4149170	SLC22A6	Chromosome 11	62984817	C > T
rs11568626	SCL22A6	Chromosome 11	62984542	C > T
rs11231809	SCL22A11	Chromosome 11	64535478	T > A
rs73885319	APOL1	Chromosome 22	36265860	A > G
rs60910145	APOL1	Chromosome 22	36265988	T > G
rs71785313	APOL1	Chromosome 22	36265996-36266005	delTTATAA

### Statistical analysis

Descriptive results of continuous variables will be expressed as medians and interquartile ranges. Continuous variables will be tested for normality using the Shapiro–Wilk test and compared using the student’s *t* test or Wilcoxon rank sum test, as required. For the comparison of proportions, the Chi-square test will be used, with Fisher’s corrections applied when needed. Multivariate logistic regression analyses will be performed to identify factors associated with KTD. Parameters with significant *p*-values in the univariate analysis will be entered into a stepwise multivariate analysis. Deviations from Hardy-Weinberg equilibrium of individual alleles and differences in allele frequencies between the two groups will be evaluated by either the chi-square test or Fisher’s exact test where appropriate. Statistical comparisons for genotype frequencies between persons with KTD and those without KTD will be made by the chi-square test or Fisher’s exact test. Associations between allele sets or haplotypes and the risk of TDF-induced KTD will be estimated by computing odds ratios and 95% confidence intervals from multivariable logistic regressions. This analysis will include adjustments for demographic characteristics (age, sex, and BMI), baseline eGFR, duration of HIV infection, protease inhibitor therapy, and other antiretroviral treatment. All statistical analyses will be conducted using Stata 12 and R statistical software. *P* values < 0.05 will be considered statistically significant. Methods for controlling the false discovery rate and Bayesian analysis under shrinkage priors will be used when reporting the results of multivariable logistic regression.

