### Setting and study population

The study will be conducted at the Department of Internal Medicine, Ladoke Akintola University of Technology Teaching Hospital (LTH), Osogbo, Nigeria and the Department of Internal Medicine Research Laboratory, University of the Witwatersrand, Johannesburg, South Africa. Participants will be recruited from ART clinics in Nigeria including LTH (Osogbo), Jaleyemi Catholic Hospital (Osogbo), Osun State Hospitals (Asubiaro, Ede, Ikire, Iwo, and Ila Orogun), Adeoyo State Hospital (Oyo State) and Seventh Day Adventist Hospital (Ile-Ife).

For the case-control phase of the study, PLWHIV on a TDF regimen under regular follow up for at least 3 months at the ART clinics who developed proximal KTD will be designated as cases. Research has shown that the median time to nephrotoxicity after TDF initiation is 3.6 months [8], hence, the rationale for a minimum of 3-months on TDF. The controls will be PLWHIV on a TDF regimen under regular follow up for ≥3 months at the ART clinics showing none of the abnormalities suggesting proximal KTD. The cases will be matched one-to-one to controls by gender, age (+/− 5 years), and TDF duration (+/− 3 months) and will be done on an ongoing basis during recruitment of study participants.

Participants meeting the inclusion criteria will be PLWHIV, aged 18 years and above, receiving TDF-containing therapy, on regular follow up for a minimum of 3 months with a viral load of less than 200 copies/ml. The rationale for the use of 3 months cut off point for the duration of tenofovir treatment was based on the results of a previous study by Brennan et al. [8] that showed that the median time to nephrotoxicity after initiation of TDF was approximately 3 months.

The following individuals will be excluded from the study: Individuals with incomplete history of antiretroviral treatment, including HIV treatment status (either treatment-naïve or experienced), date of commencement of ART and combination of ART); persons who are pregnant or lactating; persons with an estimated glomerular filtration rate (eGFR) < 60 ml/min/1.73m^2^ (eGFR will be calculated by Chronic Kidney Disease Epidemiology Collaboration [CKD-EPI] from serum creatinine estimated during the month enrolled in the study); persons with glomerulonephritis, including IgA Nephropathy and Lupus Nephritis; heart failure (NYHA 3 & 4), malignancy and non-Nigerians.

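### The case-control phase is pair-matched on sex, age and TDF duration, but the stated analysis ignores the pairs and omits TDF duration, so odds ratios for duration-related factors in the matched set shrink toward 1

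*Protocol article*

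**What the plan says.** Design (Setting and study population): "The cases will be matched one-to-one to controls by gender, age (+/− 5 years), and TDF duration (+/− 3 months" is the matching rule, applied while recruitment proceeds. Sample size and power analysis plans 400 cases and 400 controls, with a one-to-one ratio in Table 1.

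Analysis (Statistical analysis):
- Genotypes: "Statistical comparisons for genotype frequencies between persons with KTD and those without KTD will be made by the chi-square test" or Fisher's exact test.
- Alleles: "differences in allele frequencies between the two groups will be evaluated by either the chi-square test or Fisher’s exact test where appropriate".
- Allele sets and haplotypes: odds ratios "will be estimated by computing odds ratios and 95% confidence intervals from multivariable logistic regressions".
- Covariates: "This analysis will include adjustments for demographic characteristics (age, sex, and BMI), baseline eGFR, duration of HIV infection, protease inhibitor therapy, and other antiretroviral treatment".
- Risk factors: a stepwise model, entered only by variables that are significant univariately.

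The section mentions no conditional logistic regression, McNemar test or matched set. Two of the three matching factors are in the covariate list. TDF duration is not. Duration of HIV infection is listed, but it is a different variable.

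**The concern.** In a case-control study, matching on a factor does not remove it from the analysis. It forces controls to share the cases' distribution of that factor, and so of anything correlated with it. Unless the analysis conditions on the pairs or adjusts for the factor, the odds ratio of a correlated exposure moves toward 1. This happens whichever sign the correlation has.

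The unhandled factor here is TDF duration. The article's Background lists length of therapy among the reported risk factors for KTD. Other parts of treatment history (protease-inhibitor use, other antiretrovirals, time since HIV infection) plausibly track time on TDF. The article hypothesises that protease inhibitors add to susceptibility, and its Discussion plans to study interactions between risk factors and genotype. If such effects are estimated in the 400 pairs with the stated model, the main effects would be understated.

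The stepwise rule would not bring TDF duration back. Matching within 3 months leaves it nearly equal in the two groups, so it would not be significant univariately.

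**Working it through.** **Step 1: reproduce the plan's own figure.** Inputs from Sample size and power analysis: dominant model, MAF 0.19, alpha 0.003 (taken as two-sided), power 80%, KTD 13%, ratio 1:1.

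- Carrier frequency: 1 − (1 − 0.19)² = 0.344.
- (z₀.₉₉₈₅ + z₀.₈₀)² = (2.968 + 0.842)² = 14.51.
- With 13% as the risk in non-carriers and OR 1.75, risk in carriers = 0.207. Carrier frequency is then p₁ = 0.455 in cases and p₀ = 0.323 in controls.
- Discordant pairs: a = p₁(1 − p₀) = 0.308 and c = p₀(1 − p₁) = 0.176.
- Expected likelihood ratio per pair: 2[a·ln(2a/(a+c)) + c·ln(2c/(a+c))] = 0.03647.
- Pairs needed: 14.51 / 0.03647 = 397.8. Table 1 states 398.

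| OR | Table 1 | 1:1 conditional | Unmatched likelihood ratio |
|---|---|---|---|
| 1.25 | 2531 | 2530.7 | 2527.1 |
| 1.50 | 760 | 759.6 | 756.0 |
| 1.75 | 398 | 397.8 | 394.2 |
| 2.00 | 260 | 259.8 | 256.2 |
| 2.25 | 191 | 190.7 | 187.0 |
| 2.50 | 150 | 150.2 | 146.6 |
| 2.75 | 124 | 124.2 | 120.5 |
| 3.00 | 106 | 106.1 | 102.4 |

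All eight rows agree with the conditional calculation after rounding. The unmatched version is about 4 low throughout. If 13% is read as overall prevalence, the figures at OR 1.75 are 396.5 (conditional) and 392.8 (unmatched). So the sample size fits a matched analysis best, and the Statistical analysis section does not specify one.

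**Step 2: size of the bias.** The document does not say how strongly any exposure is associated with TDF duration, so the values below are assumptions. True OR for the exposure is 1.75, with pairs matched on TDF duration.

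- Column A is an exact calculation that ignores the pairs, with KTD OR 1 to 2 per SD of TDF duration.
- Columns B to D are large simulations with KTD OR 1.5 per SD. HIV duration is correlated 0.7 with TDF duration (assumed).

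| Exposure OR per SD of TDF duration | A: pairs ignored, no adjustment | B: HIV duration adjusted | C: TDF duration adjusted | D: discordant-pair OR |
|---|---|---|---|---|
| 1 | 1.75 | 1.73 | 1.73 | 1.74 |
| 1.5 | 1.72 | 1.73 | 1.74 | 1.74 |
| 2 | 1.66–1.67 | 1.72 | 1.77 | 1.77 |
| 3 | 1.57–1.59 | 1.68 | 1.77 | 1.78 |
| 5 | 1.47–1.49 | 1.59 | 1.75 | 1.77 |

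Columns C and D scatter around 1.75 by about 0.03, which is simulation error. With a negative exposure-duration association the column A value is also below 1.75: 1.66 at strength 2 and 1.48 at strength 5.

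**Step 3: does it reach the SNPs?** Exact calculation, pairs ignored, in a model with SNP, exposure and their product. Assumptions: SNP independent of TDF duration, carrier frequency 0.344, exposure prevalence 20%, KTD prevalence 13%, KTD OR 1.5 to 2 per SD, exposure OR 1 to 5 per SD.

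- SNP OR, true 1.75: returns 1.75 to 1.76.
- Interaction OR, true 1.00: returns 1.00.
- Interaction OR, true 2.00: returns 1.99 to 2.04.
- Exposure OR, true 1.75 with no interaction: falls to about 1.49 to 1.51 at exposure OR 5 per SD.

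Only the main effect of the duration-related exposure moves.

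**The case against.** The strongest defence is that the case-control phase exists to test SNPs. The Abstract gives prevalence and risk factors to the 3000-person cross-sectional phase and SNP associations to the matched phase. Germline SNPs have no evident link to time on TDF. In the allele and haplotype model, protease-inhibitor therapy and HIV duration appear as adjustments, and adjusting for HIV duration already recovers part of the bias. The t test, Wilcoxon, general chi-square and stepwise sentences are not tied to a phase and suit the unmatched 3000. The covariate list is introduced as what the analysis will include, so a fuller plan could add to it.

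Most of this stands, and it limits the point. A reader might infer that the primary SNP odds ratios, or the gene-by-factor interactions, are biased. Step 3 does not support that for SNPs unrelated to TDF duration. Nor does the text support a claim that every stated test is misapplied, or that the protease-inhibitor hypothesis must fail: Study design lists protease inhibitors among the whole-study risk factors, and the unmatched phase can address them. For such SNPs, genotype is not correlated within pairs through TDF duration, so ignoring the pairs does little to the standard error on that account.

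What remains is that the article does name its genotype tests, its model and its covariates, and they do not fit the matching that it also fixes. This is a stated choice, not detail left for later.

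**Conclusion.** The mismatch is real and of moderate importance: it should be fixed. Odds ratios taken from the matched set for factors related to TDF duration are biased toward 1. A true 1.75 becomes about 1.7 to 1.5 for assumed exposure odds ratios of 2 to 5 per SD of TDF duration, and about 1.72 to 1.59 if HIV duration is adjusted for with an assumed correlation of 0.7. These associations are not in the document. If an exposure is unrelated to TDF duration, there is no bias.

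SNP and gene-by-factor odds ratios are essentially unaffected while the SNP is unrelated to TDF duration. That could fail if genotype influences who stays on TDF, but the document gives no evidence either way. The cross-sectional analysis of 3000 is not matched and is not touched. The agreement of Table 1 with a conditional calculation suggests that a matched analysis was in mind at planning. It does not prove it.

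**What to change.** For the case-control phase, state one of two analyses:

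1. Conditional logistic regression with the pair as stratum for all odds ratios, and McNemar-type tests for simple comparisons. This also fits the Table 1 calculation.
2. Unconditional logistic regression with sex, age and TDF duration all forced in, outside any stepwise selection. Age and sex are already listed, so this adds one covariate.

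Keep the independent-group tests and the stepwise risk-factor model for the cross-sectional phase, and say so. Choose before the case-control data are analysed, so that matched and unmatched results are not compared first.

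The cost is analysis wording. At the plan's average MAF, OR 1.75 and alpha 0.003, about 398 pairs are needed for 80% power and 400 are planned. That margin is thin, and conditional analysis loses a whole pair when one member lacks a genotype or covariate. The unconditional option avoids that loss of the partner.
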